## Sampling and recruitment

Patients attending the Redcliffe Post-ICU clinic will be informed about the trial of an inclusion of an early psychiatric review as part of the clinic following their completion of standard clinic cares (see Appendix 1 for the Standard Operating Procedures).

If the patient expresses interest in the study, they will be provided written and verbal information regarding the purpose and aims of the study and invited to ask any questions they have about the study before being invited to participate. Potential participants will not be aware if they have been randomised to the control or intervention arm at this stage.

The potential participant will be provided multiple opportunities to discuss the study with members of staff not involved in the study. Information will be provided in writing and verbally before the patient is invited to consent to participate in the study.

A patient information and consent form will be provided. People who agree to participate will complete the written consent form before any data collection takes place. Patients who consent to participate will be randomised using a simple randomisation schedule. Participants randomised to the intervention arm will be offered an appointment with the psychiatrist in addition to standard clinic cares, whereas participants randomised to the control arm will receive standard clinic cares only.

For those attending their appointment over the phone, verbal consent will be obtained and witnessed. People who give consent will give permission for research staff to access data from their clinical records and will complete a series of questionnaires examining their premorbid function, experiences in ICU and their subsequent recovery across a range of domains.

To monitor recruitment, a re-identifiable log will be kept that will document patients eligible for approach, and subsequent contact.

Participants will be able to withdraw from the study at any time. If a participant that has been randomised to receive the early psychiatric intervention chooses to withdraw consent, they will receive the standard cares provided by the clinic without the intervention, and any collected data will be withdrawn from the study.

Six months after clinic presentation, research staff will contact all participants to offer a follow-up appointment either in the clinic or by phone and conduct the follow-up survey as described below. Participants will be invited to continue and will have the opportunity to withdraw from the study before this additional data is collected.

At the 6-month follow-up timepoint when potential participants do not respond to the first contact attempt, research staff will attempt contact again one week later. Potential participants who remain uncontactable after the second attempt will be considered lost to follow-up and not contacted again.

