# Aims and objectives

The primary objective of this pilot RCT study is to:

1. To evaluate feasibility (cost and practicability) and acceptability of an early psychiatric intervention in a post-ICU clinic.

Secondary Objectives are:

1. Assess the impact of early psychiatric assessment and provision of referral options on self-efficacy and rates of health service access for patients requiring psychological intervention post-ICU
2. Measure the change in symptom severity for anxiety, depression, and PTSD between presentation, and 6 months after presentation.
3. Measure the impact on work, income, and independence in activities of daily living (ADL)

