## Post Appointment Questionnaire

To address the primary outcome, the **Post Appointment Questionnaire** is an 8 item self-reported acceptability measure that has been specifically developed for this study. It has been adapted from similar surveys used in previous acceptability studies. Questions focus on whether the participant found their appointment helpful, how confident they feel about managing any psychological symptoms they have or may develop, and how optimistic they feel about their recovery.

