## Statistical analysis

The demographics and results of the Baseline Outcome Measures Bundle will be described using proportions and associated 95% confidence intervals and compared between intervention and control groups to check the integrity of the randomisation.

Responses to the Post Appointment Questionnaire will be assumed to be additive and averaged to produce the primary outcome measure. Differences between groups will be assessed using t-test.

Changes in secondary outcome measures between baseline and 6 months will be compared between intervention and control groups to identify any clinically and statistically significant differences using ANCOVA regression with patients results at baseline fitted as a covariate. The model residuals will be checked to look for outliers and bi-modality. Leave-one-out sensitivity analyses will be used to look for patients that strongly influence the results.

Two-by-two tables will be created of the predicted and observed PICS, together with statistics on sensitivity, specificity, and negative and positive predictive value. Models will be checked for influential observations and outliers. The results will be reported using the EQUATOR TRIPOD checklist to ensure completeness and transparency[29].

The overall characteristics of the sample will be described using summary statistics. This will help inform the generalisability of our results. The number of patients approached and consented will be tabulated, together with the number who dropped out or died.

.

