**Consent:**

All potential participants will receive information about the study in writing and verbally and have the opportunity to ask any questions they have and discuss their participation with a person of their choosing should they wish. Potential Participants will be allowed as much time as they need to consider participation, and participants can decline assessments or withdraw from further participation at any time.

The research team decided for simple randomisation prior to consent for the following reasons:

Minimise departure from standard practice for participants not participating in the study.

In BAU, patients are not invited to the post-ICU clinic while still in ICU, and this is instead discussed several weeks after discharge to allow some time for rest and recovery prior. Informed consent while still in hospital would require participants to make a decision about the post-ICU clinic much earlier in their recovery trajectory than usual.

Respect the patient’s right to distributive justice

The research team were concerned that because ICU clinical staff cannot be blinded to when the intervention is available, a non-structured approach to appointment allocation risks unconscious bias from staff. While a departure from BAU, simple randomisation would ensure that patients’ rights to equal opportunity in care and to participate in research is respected.

Respect the patient’s right to sufficient opportunity to consider participation prior to consent

In BAU, participants are invited to attend the post-ICU clinic via telephone several weeks after discharge. The research team felt that invitation to participate, or even to randomisation in this setting would not provide the patient sufficient time to reflect and seek advice before making a decision.

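### Automatic removal of collected data on withdrawal, with the exclusion of consented participants who lack baseline or 6-month data, can bias the acceptability outcome; one rule for both arms is needed

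*Protocol*

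**What the plan says.** Three parts of the protocol decide what happens to a leaver's data.

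- **Sampling and recruitment.** Everyone has the right to leave: "Participants will be able to withdraw from the study at any time". A consequence for data is then given for one arm: "If a participant that has been randomised to receive the early psychiatric intervention chooses to withdraw consent", that person receives standard clinic care without the intervention, and "any collected data will be withdrawn from the study". At the 6-month contact all participants "will have the opportunity to withdraw from the study before this additional data is collected".
- **Exclusion criteria.** A person who consents but does not supply baseline or 6-month data is excluded, whichever arm they are in.
- **Ethical Considerations, Consent.** Here "participants can decline assessments or withdraw from further participation at any time". Nothing is said about removing data already given.

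The outcome affected is the primary one. The primary objective is "To evaluate feasibility (cost and practicability) and acceptability of an early psychiatric intervention in a post-ICU clinic". The Post Appointment Questionnaire "is an 8 item self-reported acceptability measure that has been specifically developed for this study". Its items are averaged into the primary outcome measure, and "Differences between groups will be assessed using t-test". The Follow-up Survey section has it repeated at 6 months, so a first set of answers exists before the 6-month withdrawal point. The Statistical analysis section also tabulates how many participants dropped out or died.

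**The concern.** In an acceptability trial, people who leave because the intervention was unwelcome carry information about the primary question. A rule that automatically removes what they have already reported selects the scores on a variable likely to be related to the outcome. The rule is written for the intervention arm alone and does not sit with the Consent section, so staff could handle the same event differently by arm or by which section they read. It also gives no separate route for someone who declines the psychiatrist but is willing to be followed up.

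The loss may be irreversible: once data have been withdrawn, no analysis can restore them. With about 15 per arm, two or three removals are 13% to 20% of an arm (2/15 and 3/15).

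**Working it through.** **Step 1. What the text does to each kind of leaver.** The protocol states no figure for withdrawals, so there is nothing to reproduce. Reading the three sections together:

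| Event | Intervention arm | Control arm |
|---|---|---|
| Declines the psychiatrist, accepts follow-up | No rule stated | Does not arise |
| Withdraws consent before the first questionnaire | Data removed; no score exists to lose | No data rule; excluded for lack of 6-month data |
| Withdraws consent at the 6-month contact | First questionnaire score removed | No data rule; excluded for lack of 6-month data |
| Cannot be contacted at 6 months | Excluded for lack of 6-month data | Same |
| Withdraws consent after giving 6-month data | Data removed | No data rule |

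If the exclusion criterion is applied literally, most control leavers are removed as well. The arms then differ by rule only in the last row, or wherever that criterion is not enforced. In both arms, however, a first questionnaire score already in hand is lost when a person leaves before 6 months. Correcting the withdrawal sentence alone would leave that loss in place.

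**Step 2. Size if leavers score somewhat low.** Inputs: 15 per arm (Participants and sample calculation). Assumptions: k leavers whose scores average m SD below their full arm's mean, with no true difference between arms. The mean of those who remain rises by

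shift = k × m / (15 − k).

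- k = 1: 0.5/14 = 0.04 SD; 1.5/14 = 0.11 SD.
- k = 3: (3 × 0.5)/12 = 0.13 SD; (3 × 1.5)/12 = 0.38 SD.

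The bias in the between-arm difference is the intervention-arm shift minus the control-arm shift. If both arms lose the same number of people, equally far below their own mean, the two shifts cancel. The figures above therefore assume no corresponding control losses.

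**Step 3. Worst case.** Simulation with 40,000 runs, normal scores, 15 per arm, no true difference and a two-sided t-test at an assumed 5% level. The k lowest intervention scores are removed and no control scores.

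| k removed | Bias (SD) | Two-sided rejection | Significant in favour of intervention |
|---|---|---|---|
| 0 | 0.00 | 4.9% | 2.4% |
| 1 | 0.12 | 6.8% | 5.5% |
| 2 | 0.23 | 10.5% | 9.8% |
| 3 | 0.33 | 15.5% | 15.2% |

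**Step 4. After the fix.** If data up to withdrawal are kept in both arms, this corresponds to the k = 0 row: no bias from this source, and a rejection rate of about 5%.

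**The case against.** A reader might infer that the protocol erases those who find the intervention unacceptable, and does so in one arm only. The documents do not support that.

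- The exclusion for missing baseline or 6-month data covers both arms, so control leavers are largely removed too.
- The one-arm reading is partly silence. The sentence explains what care an intervention participant gets after withdrawing, which a control does not need to be told. Nothing says that control data are kept. The consent form is not in the available copy, so a general rule there cannot be ruled out.
- The trigger is withdrawal of consent. Declining the psychiatrist is not said to count as that, and a dissatisfied participant who stays in is scored.
- The wording about standard care without the intervention most naturally describes leaving before the psychiatrist is seen, when no score about that appointment exists.
- Dropouts are tabulated, so leavers remain visible as a count.
- Removing data at a participant's own request is legitimate.

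A reader might also take the 10.5% and 15.5% rejection rates as the expected error of the trial. They are not: they require that the leavers are exactly the lowest scorers and that no controls are removed. The protocol states no significance level and ties no decision to the t-test.

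These points limit the size and certainty of the bias. They do not remove the problem. The automatic deletion is written, it reaches completed questionnaires at the 6-month withdrawal point, and it does not sit with the Consent section. The dropout count is not specified by arm or reason and does not restore the scores.

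**Conclusion.** The point holds as a defect in stated rules. The withdrawal sentence and the missing-data exclusion together discard primary-outcome scores already collected from people who leave, and the sections do not agree on what withdrawal means for data. The direction favours the intervention if its leavers rated it lower and control losses do not offset this.

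The size cannot be fixed from the protocol, which gives neither a withdrawal rate nor a score SD. A plausible range for one leaver of 15 is 0.04 to 0.11 SD. The 0.23 to 0.33 SD for two or three leavers is a worst case. If nobody leaves, or leaving is unrelated to the score, there is no bias.

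This should be fixed, and preferably before data are removed. It does not invalidate the design.

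**What to change.** 1. Write one rule for both arms with three separate events: declining or stopping the psychiatric appointment (the participant stays in the allocated arm and in follow-up), stopping follow-up, and withdrawing consent for use of data.
2. Keep and analyse data collected up to withdrawal unless the participant asks for removal.
3. Delete the exclusion criterion for consented participants without baseline or 6-month data, so that they are analysed for the data they gave. Without this, item 2 has little effect.
4. Reconcile Exclusion criteria, Sampling and recruitment, and Consent, and make the consent form match.
5. Report declines, withdrawals and deletion requests, with reasons and by arm, as a separate acceptability and feasibility result. Do not recode declines into the questionnaire score: it is an average with no category for refusal, and people may decline for reasons unrelated to acceptability.

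The cost is a wording change to the protocol and consent form, and possibly a less favourable acceptability result.

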**Participants and sample calculation:**

Data will be collected from a sample of approximately 30 patients attending the Redcliffe ICU follow-up clinic over a 12-month period, with 15 randomised to the control and intervention arms respectively.

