**Exclusion criteria:**

- Patients whose life expectancy at discharge is estimated by their clinical team to be less than 6 months
- Unable or unwilling to provide consent to participate for the duration of the study
- Provide consent, but do not provide baseline or 6-month follow-up data
- Unlikely to remain contactable for 6 months after their clinic appointment

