## Follow-up Survey

At the 6-month timepoint, participants will repeat the Post Appointment Questionnaire, PICS Measures (including HADS and EQ5D-5L), Life Events Checklist, Generalised Self Efficacy Screen and Patient Employment Information Questionnaire, as well as the Health Services Use Questionnaire described below. The follow-up Survey can be found in Appendix 3.

This **Health Services Use** Questionnaire has 11-items and been adapted from a questionnaire utilised in a recent injury vulnerability study[26]. It explores how often the participant has attended a range of clinical, allied health and alternative health services, whether these services were helpful for their mental health, and for those think they needed more help from health professionals than was accessed, the main reason they didn’t get this help.

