## 6 Month Outcomes Follow-up

At the completion of data collection at the clinic appointment, permission will be sought to contact participants again 6 months after their appointment and participants will be asked to nominate a preferred form of contact.

A member of the research team will contact the participant via their preferred contact method approximately 6 months after their clinic appointment.

After providing consent to continue participating, the participant will complete the outcome measure bundle again.

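### The 6-month contact rule stops after two attempts a week apart, so some follow-up data in a trial of about 30 will be lost avoidably and possibly in relation to outcome

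*Protocol*

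**What the plan says.** The rule is in the Protocol, Sampling and recruitment. When the first 6-month contact gets no response, "research staff will attempt contact again one week later". It then closes: "Potential participants who remain uncontactable after the second attempt will be considered lost to follow-up and not contacted again". The text says potential participants, but by this stage they have consented and been randomised.

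Other sections bear on the rule:

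- **6 Month Outcomes Follow-up:** permission for the later contact is sought at the clinic visit, and "participants will be asked to nominate a preferred form of contact".
- **Inclusion and Exclusion criteria:** people must be likely to be contactable at 6 months, and those unlikely to remain so are excluded.
- **Participants and sample calculation:** the sample is "approximately 30 patients attending the Redcliffe ICU follow-up clinic over a 12-month period", "with 15 randomised to the control and intervention arms respectively". No allowance for dropout is stated.
- **Follow-up Survey:** "At the 6-month timepoint, participants will repeat the Post Appointment Questionnaire", together with the PICS measures, self-efficacy, employment and health-service use.
- **Statistical analysis:** "Changes in secondary outcome measures between baseline and 6 months will be compared between intervention and control groups". Dropouts and deaths are to be tabulated.

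No section adds further attempts or an alternative contact, and none gives a reason for stopping at two.

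**The concern.** The limit is a fixed operational rule that forbids recovering data, so it is not a detail that an analysis plan could settle later. All 6-month outcomes depend on this one contact. Routine clinic review is at around three months (Setting), and no other 6-month source is described.

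Two attempts seven days apart are close together. A single readmission, a spell of illness or a short absence can cover both. The Participant safety section itself expects that some people will have become unwell or died before the next contact. Illness is close to what HADS, PCL-5 and EQ-5D-5L measure, so those who are missed may differ on the outcome from those who are reached.

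At stake are the precision of the secondary comparisons, the risk of outcome-related loss, and the retention figure that later studies would take from this pilot. A figure obtained under a two-attempt ceiling may understate what is achievable.

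**Working it through.** **Plan's own figure.** The size of about 30 (15 per arm) is stated without a significance level, power, target difference, standard deviation or dropout rate. It cannot be reproduced, and there is no planned loss to compare with.

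**Inputs.** From the Protocol: N = 30 and k = 2 attempts. Assumed, because the Protocol gives no contact rate: a probability p that one attempt succeeds, taken from 0.5 to 0.8. Comparison: k = 4 attempts.

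**Step 1: expected loss with independent attempts and the same p for everyone.** Expected number lost = 30 × (1 − p)^k. The standard error (SE) of a between-arm contrast varies as 1/√(number remaining), so

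SE ratio (two attempts to four) = √{[1 − (1 − p)^4] / [1 − (1 − p)^2]} = √[1 + (1 − p)^2].

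| p | lost of 30, k = 2 | lost of 30, k = 4 | SE ratio |
|---|---|---|---|
| 0.5 | 30 × 0.25 = 7.5 | 30 × 0.0625 = 1.9 | √1.25 = 1.12 |
| 0.6 | 30 × 0.16 = 4.8 | 30 × 0.0256 = 0.8 | √1.16 = 1.08 |
| 0.7 | 30 × 0.09 = 2.7 | 30 × 0.0081 = 0.2 | √1.09 = 1.04 |
| 0.8 | 30 × 0.04 = 1.2 | 30 × 0.0016 = 0.05 | √1.04 = 1.02 |

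**Step 2: allow some people to be persistently hard to reach.** Let p vary between people as a beta distribution with mean 0.6 and a + b = 2, so a = 1.2 and b = 0.8.

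- Two attempts: loss = (0.8 × 1.8)/(2 × 3) = 0.24.
- Four attempts: loss = (0.8 × 1.8 × 2.8 × 3.8)/(2 × 3 × 4 × 5) = 0.128, about 13%.
- SE ratio = √(0.872/0.76) = 1.07.

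Loss is roughly halved here. With the same mean contact probability but no variation between people (p = 0.6 in the table), it falls from 16% to under 3%.

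**Step 3: what the loss does to precision.** For an unadjusted difference in means, the 95% confidence half-width is t(0.975; 2n − 2) × √(2/n) SD, with n completers per arm.

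- n = 15: 0.75 SD
- n = 12 (20% lost): 0.85 SD
- n = 10 (33% lost): 0.94 SD

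**Step 4: what differential loss could do.** If missing patients differ from observed ones by D SD in both arms, the bias is (f2 − f1) × D, where f1 and f2 are the fractions lost in each arm. For illustration, with 10% and 30% lost and D = 0.5 to 1.0, the bias is 0.20 × 0.5 = 0.1 SD to 0.20 × 1.0 = 0.2 SD. With equal loss and the same D in both arms it is zero. Nothing in the Protocol says which case will apply.

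**The case against.** The best defence is that the cap is a deliberate and respectful choice. Participation is voluntary, follow-up contact is to be handled sensitively, and two unanswered contacts may be a quiet refusal. The eligibility criteria already select people likely to be reachable, and each participant names a preferred route, so p may be near the top of the range and the loss about one patient. Much of this stands, and it limits the size of the point. It does not justify an absolute bar on a third attempt to people who gave permission for this contact, because stopping on refusal protects them as well.

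Some stronger readings are tempting but not supported:

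- **That both attempts must use one route, or be telephone calls.** The rule names no route, and the nominated form of contact need not be a call.
- **That loss will depend on arm.** The extra contact at 4-6 weeks (Intervention Follow-up) goes only to patients in whom an intervention was initiated, not to the whole intervention arm. A difference between arms is possible but speculative.
- **That more attempts would remove the bias.** Step 2 shows that a hard-to-reach group largely remains.
- **That the primary outcome is at risk.** The acceptability questionnaire is first linked to the appointment; only its repeat needs the 6-month contact.

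The exclusion criterion "Provide consent, but do not provide baseline or 6-month follow-up data" may turn a missed contact into removal from the trial. That is a separate defect, which changing the number of attempts does not cure, and it adds no weight here.

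**Conclusion.** The point holds at minor to moderate severity. The two-attempt stop is explicit, nothing else in the Protocol relaxes it, and it governs the only described source of 6-month data in about 30 patients. Some of the resulting loss is avoidable and may be related to outcome.

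The size rests on assumed contact probabilities. Moving from two attempts to four would recover about 1 to 6 of 30 patients over p = 0.8 to 0.5 (1.2 − 0.05 = 1.15; 7.5 − 1.9 = 5.6). The present rule makes standard errors about 2% to 12% larger. The 12% is the unfavourable end of that range and should not be quoted alone. With contactability varying around a mean of 0.6, the figure is about 7%. The effect falls on the secondary outcomes, the repeat acceptability questionnaire and the retention estimate. The amount of bias cannot be determined from the Protocol.

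**What to change.** Replace the two-attempt limit in Sampling and recruitment with, for example:

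- up to four attempts over about four weeks, on different days and at different times;
- the nominated route first, then a second route that the participant agreed to at the clinic visit;
- an immediate stop if the participant declines;
- classification as lost to follow-up only after these steps;
- the number of attempts and the losses reported by arm.

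The GP should be used for tracing only if the consent form covers it. The Inclusion criteria ask for a GP so that the team can correspond about the intervention, which is a different purpose.

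The cost is some staff time and slightly more contact burden for a few people, and a small change of wording for the ethics committee. It should be made before 6-month follow-up begins, since contacts missed under the present rule are hard to recover afterwards.
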